### Assignment to treatment group

At each study site participants are randomly assigned to either Standard Care or Sustained Care by research staff in a 1:1 fashion using permuted blocks of 8. Randomization is stratified into five groups: four strata were created by crossing daily cigarette consumption (<10 versus ≥10 cigarettes per day) with admitting service (cardiac vs. non cardiac), and a fifth stratum was created for HIV-infected patients. A series of sealed manila envelopes was created for each stratum, with the randomization ID on the outside of the envelope and the study arm assignment inside the envelope. The research assistant informs the participant and initiates the protocol for the assigned study arm. The study is not blinded to participants or to research staff, but enrollment and follow up activities are conducted by research staff members not involved with recruitment.

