#### Pharmacotherapy

A free 1-month supply of FDA-approved smoking cessation pharmacotherapy is delivered to the participant prior to discharge. Cessation medication options include NRT (nicotine patches, lozenges, or gum), bupropion, or varenicline. Either a single medication, or more commonly, a combination of medications is prescribed (e.g., nicotine patch and lozenge). The participant chooses the pharmacotherapy, guided by the hospital tobacco counselor, who considers the participants’ number of cigarettes smoked daily, time to smoking first cigarette in the morning, participant preference, past cessation medication experience, and medical contraindications. The hospital physician writes the prescription which is filled by the hospital pharmacy or, at NSMC, a community pharmacy. All participants receive a handout with information on proper medication use, side effects, and instructions on how to obtain the two additional months of free medications through the IVR, quitline, and study staff. On rare occasions when a participant is discharged before receiving the prescribed cessation medication in hand, the research staff ships the medication using overnight delivery and calls the participant to ensure receipt of the medication.

When a participant requests a free refill of NRT, the Quit Coach asks about current medication use, reviews medication prescribed upon discharge, revisits exclusion questions, and refills the medication. An automatic delivery system from Alere’s warehouse delivers the medication within 48-72 hours. To refill a prescription-only cessation medication, a Quit Coach notifies a member of the research staff, and the study staff assesses medication use and side effects with the participant. Subsequently the research staff arranges to have the refill shipped from the pharmacy through which it was originally filled (Figure 1).

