### Data analysis

A total sample of 1350 was planned to detect a difference of 4.8% (12.8% vs. 8.0%) in the primary outcome measure, validated 7-day tobacco abstinence at 6-month follow-up, with 80% power and a 2-tailed type I error rate of .05. Analysis of study data will use an intention-to-treat approach. In the primary analysis, subjects lost to follow-up due to all circumstances will be coded as smokers for smoking status outcomes. A sensitivity analysis will be conducted based on different assumptions on missing data [33]. Multiple imputation techniques will also be used to take into account uncertainty due to missing data.

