#### Secondary outcomes

For all outcomes measured at 1, 3, and 6 months, cross-sectional analyses will be used to compare between study groups. Secondarily, a longitudinal analysis using Generalized Estimating Equations (GEE) techniques will be conducted to assess the overall impact of Sustained Care by including data from all follow-up times. Similar to the primary outcome, regression models will be used to compare treatment group adjusting for site and any important confounders; these will be logistic regression for dichotomized outcomes (e.g. self-reported abstinence, any counseling/medication use), and Poisson regression for the number of event outcomes (e.g. number of counseling contacts, number of emergency room visits, number of hospital readmissions). Survival analysis techniques will be used to analyze the duration-related outcome variables (self-reported duration of continuous abstinence and duration of post-discharge medication use). Kaplan-Meier curves will be used to estimate the median duration of tobacco abstinence and medication use. Cox proportional hazard models will examine intervention effects adjusting for potential confounding factors.

*Cost-effectiveness* will be assessed using cost per quit as the main outcome in order to compare our results with other published studies [22,34,35]. The incremental costs per quit are estimated as follows: (Total costs of Sustained Care – Total costs for Standard Care)/(Total successful quits at six months for Sustained Care – Total successful quits at six months for Standard Care) where successful quits are defined according to our primary outcome of 7-day point prevalence abstinence. The major costs tracked in the study are as follows: (1) initial counselor assessment pre-discharge, which includes counselor chart review, counseling, and medication recommendations; (2) Quit Coach medication assessment and cessation support post-discharge; (3) IVR service; and (4) medication costs, including dispensing and delivery. For both study arms, we will track the portion of counseling and medication costs paid for by participants out of pocket and/or by insurance.

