## Trial status

A total of 1,359 participants were enrolled in the study between December 2012 and July 2014. The follow-up of these participants is in progress. Enrollment data from the HH2 study can be compared to enrollment data from the HH1 study to assess whether the HH2 study met its goal of enrolling a higher proportion of hospitalized smokers by broadening the eligibility criteria to permit enrollment of smokers with comorbid alcohol or other substance abuse. In the HH2 study, 1416 (72%) of the 1959 smokers who were fully screened met eligibility criteria and 1359 (69%) were enrolled. By comparison, in the HH1 study, only 432 (48%) of the 904 smokers who were fully screened met eligibility criteria and only 397 (44%) enrolled. In the HH2 study only 23 (1%) of 1959 patients were excluded for alcohol or other substance abuse, compared to 254 patients (28%) of 904 patients excluded for these reasons in the HH1 study. The HH2 study sample also included a higher proportion of smokers with HIV infection (4.5% [n = 61] vs. 1% [n = 4] in the HH1 study). Thus, relaxing the restriction on enrolling smokers with non-tobacco substance abuse in the HH2 study produced a sample that was more representative of all hospitalized smokers than had been recruited into the HH1 study.

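### Cost per quit is defined from arm totals, which is exact only for arms of equal size; the error is about 2% or less at the planning rates and is removed by using per-participant means

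*Protocol article*

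**What the plan says.** Under Data analysis, Secondary outcomes, the article makes cost per quit the main cost-effectiveness outcome, so that it can be compared with published studies. The formula begins "The incremental costs per quit are estimated as follows: (Total costs of Sustained Care", less the total for Standard Care. The denominator is the matching difference in counts, ending "Total successful quits at six months for Standard Care) where successful quits are defined according to our primary outcome of 7-day point prevalence abstinence". Neither part is divided by the number of participants in the arm.

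Under Assignment to treatment group, allocation at each site is "in a 1:1 fashion using permuted blocks of 8", and "Randomization is stratified into five groups". Trial status reports: "A total of 1,359 participants were enrolled in the study between December 2012 and July 2014". Arm sizes are not given.

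The same cost paragraph names four major costs: the pre-discharge counselor assessment, Quit Coach medication assessment and support, the IVR service, and medication including dispensing and delivery. Under Pharmacotherapy, the Quit Coach reviews medication use when nicotine replacement is refilled. For a prescription-only product, study staff make that assessment and ask about side effects. "Subsequently the research staff arranges to have the refill shipped from the pharmacy through which it was originally filled".

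**The concern.** A ratio of differences in totals mixes the effect of the intervention with the effect of arm size. Extra participants in one arm bring their own costs, and they bring quits that would have happened anyway. The bedside session shows this plainly. Both arms receive it, so its cost should cancel, but with 684 and 675 participants nine sessions stay in the numerator. The denominator is a small difference between two counts, so it is the more sensitive part.

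The cost list raises a smaller point of consistency. The assessment that precedes a refill is costed when a Quit Coach does it and is not named when study staff do it. That staff work occurs only in the Sustained Care arm, so leaving it out can only lower that arm's cost.

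At stake is the accuracy of a secondary economic figure meant for comparison with other programs. The primary abstinence comparison is not affected.

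**Working it through.** **Inputs from the article.** Planning statement: "A total sample of 1350 was planned to detect a difference of 4.8% (12.8% vs. 8.0%) in the primary outcome measure", "with 80% power and a 2-tailed type I error rate of .05". Enrolled: 1,359, taken here as all randomized and all analysed. Strata: 5 per site × 3 sites = 15, in blocks of 8.

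**Assumed inputs.** The article gives no costs. I use $400 (Sustained) and $100 (Standard) per participant, and vary them below.

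**The plan's own figure.** The article states no cost per quit, but its sample size can be checked. For 8.0% versus 12.8%, two-sided 0.05 and 80% power, the pooled formula gives 634 per arm (1,268). With continuity correction it gives 675 per arm, or 1,350, as stated. The planning rates are therefore a sound base.

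**Algebra.** Write n, c and p for arm size, mean cost and quit proportion, with 1 = Sustained and 0 = Standard.

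- Article: (n1·c1 − n0·c0) / (n1·p1 − n0·p0)
- Per participant: (c1 − c0) / (p1 − p0)

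Cross-multiplying, the two agree only if (n1 − n0)(c0·p1 − c1·p0) = 0. That requires equal arms, or the coincidence that c/p is the same in both arms. Because 1,359 is odd, the arms cannot be equal.

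**Likely imbalance.** If a stratum ends k places into a block of 8, the arm difference has variance k(8 − k)/7. Averaged over k = 0 to 7 this is (84/7)/8 = 1.5. Fifteen strata give 22.5, so the SD is 4.74 and 1.96 × 4.74 ≈ 9. A simulation with assumed stratum sizes agrees: the absolute difference has median 3, 95th percentile 9 and 99th percentile 13.

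**Effect at the planning rates.** The per-participant value is 300/0.048 = $6,250.

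| Arms (Sustained/Standard) | Cost difference | Quit difference | Ratio | Shift |
|---|---|---|---|---|
| 680/679 | 204,100 | 32.720 | $6,238 | −0.2% |
| 679/680 | 203,600 | 32.512 | $6,262 | +0.2% |
| 684/675 | 206,100 | 33.552 | $6,143 | −1.7% |
| 675/684 | 201,600 | 31.680 | $6,364 | +1.8% |

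Other assumed cost pairs at an imbalance of 9 give −1.9%/+2.0% ($300 and $50), −1.8%/+1.9% ($500 and $100) and ±0.9% ($200 and $100, or $500 and $250).

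**Smaller effects, same costs, imbalance of 9.**

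- 11% versus 9%: $15,000 becomes $14,224 or $15,887 (−5%/+6%).
- 10% versus 9%: $30,000 becomes $26,941 or $33,939 (−10%/+13%).

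**Sampling error for scale**, with about 679.5 per arm:

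- At 12.8% versus 8.0%, SE = √[(0.128·0.872 + 0.08·0.92)/679.5] = 1.65 points, so the 95% interval is about 1.6 to 8.0 points. Holding the cost difference at $300, that is about $3,700 to $19,000 per quit. The arm-size shift is about $110.
- At 11% versus 9% the interval is about −1.2 to 5.2 points. At 10% versus 9% it is about −2.1 to 4.1. Both include zero.

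**Staff time.** Each s dollars of uncosted staff time per Sustained Care participant adds s/0.048 per quit at the planning rates. Assumed values of $5, $10 and $20 add $104, $208 and $417. The share using bupropion or varenicline and the time per refill are not given, so no actual figure follows.

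**The case against.** The strongest defence is that the design already controls the problem. Blocked 1:1 allocation keeps the arms nearly equal, and participants lost to follow-up stay in the analysis as smokers, so attrition does not unbalance the base for the quit counts. The remaining shift is negligible beside sampling error. This stands, and it limits how much the point matters. It does not make the stated formula the right one, since the exact form costs nothing.

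A reader might infer from the 10–13% figures that the economic result is at real risk. The documents do not support that. Those figures need a 1-point effect, whose confidence interval includes zero, so cost per quit would have no usable finite interval under either formula. The design caps the imbalance at 4 per stratum, so it cannot exceed 59 for an odd total. With the costs used here, 59 would shift the ratio by −10% to +14%, but it lies more than 12 SDs out (59/4.74).

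A reader might also infer that shipping is left uncosted. The fourth cost item covers dispensing and delivery, the list is offered as the major costs only, and overnight shipment after a missed discharge supply is described as rare. What remains is the staff assessment for prescription-only refills.

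Finally, one might suspect that participants lost to follow-up silently count as zero cost. The article does not say where out-of-pocket and insurance costs come from or how missing ones are handled. Such detail, like the interval method, is properly left to a fuller plan.

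**Conclusion.** The point holds in a limited form. The stated formula is exact only for equal arms, and with 1,359 participants the arms cannot be equal. At the planning rates the error is about 0.2% for a one-person difference and about 2% or less for an imbalance of 9, which is not exceeded in about 95% of allocations. These sizes rest on assumed costs, on all 1,359 being randomized and analysed, and on blocks used in sequence within 15 strata. This is a refinement of a secondary outcome. It is not evidence of a material bias.

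The staff-time gap is real but narrow. Its direction is known, since it lowers the cost of Sustained Care. Its size is not, so the documents do not support saying that Sustained Care is made to look materially cheaper.

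**What to change.** Replace the formula with: (mean cost per randomized participant, Sustained minus Standard) / (proportion quit among all randomized, Sustained minus Standard). Quits remain those of the primary outcome. This is exact at any arm size and fits the intention-to-treat approach already stated under Data analysis.

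Add one line to the cost list for study-staff time spent assessing medication use and side effects at prescription-only refills, parallel to the Quit Coach item.

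The cost is one reworded formula and one more cost component. The first change moves the result slightly in either direction, depending on which arm is larger. The second can only raise the cost per quit, by an amount to be found from the refill counts and staff time. Follow-up was still in progress when the article was written, so both changes could be made before the outcomes were known.

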## Trial status

A total of 1,359 participants were enrolled in the study between December 2012 and July 2014. The follow-up of these participants is in progress. Enrollment data from the HH2 study can be compared to enrollment data from the HH1 study to assess whether the HH2 study met its goal of enrolling a higher proportion of hospitalized smokers by broadening the eligibility criteria to permit enrollment of smokers with comorbid alcohol or other substance abuse. In the HH2 study, 1416 (72%) of the 1959 smokers who were fully screened met eligibility criteria and 1359 (69%) were enrolled. By comparison, in the HH1 study, only 432 (48%) of the 904 smokers who were fully screened met eligibility criteria and only 397 (44%) enrolled. In the HH2 study only 23 (1%) of 1959 patients were excluded for alcohol or other substance abuse, compared to 254 patients (28%) of 904 patients excluded for these reasons in the HH1 study. The HH2 study sample also included a higher proportion of smokers with HIV infection (4.5% [n = 61] vs. 1% [n = 4] in the HH1 study). Thus, relaxing the restriction on enrolling smokers with non-tobacco substance abuse in the HH2 study produced a sample that was more representative of all hospitalized smokers than had been recruited into the HH1 study.

## Discussion

The Helping HAND 2 trial tests whether a coordinated system to sustain smoking cessation treatment initiated during a hospitalization increases the proportion of hospitalized smokers who are tobacco abstinent 6 months after discharge. The program aims to achieve this by removing barriers to continued use of smoking cessation medication and counseling. It resembles the intervention that was effective in the single-site HH1 trial [12] but extends this earlier work. It tests the intervention’s effectiveness in three hospitals in two states, and the intervention provides a new real-time direct transfer from the automated call to a live smoking cessation counselor when smokers request additional assistance. HH2 also tests the intervention in a more medically and socially diverse sample that includes smokers with other substance abuse or HIV infection, vulnerable populations whose smoking prevalence exceed that of the general population. The study enrollment data demonstrate that the HH2 study succeeded in its goal of enrolling a larger proportion of smokers admitted to the study hospitals and including smokers in more vulnerable populations. Analysis of outcome data, which is still being collected, will determine whether the intervention will retain its effectiveness. If effective, this model could be adopted by U.S. hospitals to help reduce population smoking rates, thereby decreasing tobacco-related mortality, morbidity, and health care costs.

## Abbreviations

Helping HAND: Helping Hospital-initiated Assistance for Nicotine Dependence study
HH1: Helping HAND 1
HH2: Helping HAND 2
NRT: Nicotine replacement therapy
IVR: interactive voice response
TTS: Tobacco Treatment Service
e-cigarette: electronic-cigarette
CO: carbon monoxide
MGH: Massachusetts General Hospital
NSMC: North Shore Medical Center
UPMC: University of Pittsburgh Medical Center
